### Trial design

The EndParl study is designed as a prospective, multicentre, active comparator-controlled, non-inferiority randomized trial with two parallel groups and blinding of participants and outcome assessors. Randomization will occur on the day of the procedure and will be done to one of two arms on a 1:1 allocation basis. The randomization sequence will be computer-generated, and allocation concealment will be ensured by sequentially numbered, sealed opaque envelopes. This process will be carried out by an independent research coordinator, who will not be involved in the recruitment process or conduct of the trial. An unblinded physician will do the procedure but they will not be involved in assessing the outcomes. A blinded member of the research team will perform follow-up outcome assessments. Treating physicians, participants, close contacts, trial coordinators, and primary outcome analysts will be blinded to treatment allocation.

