## Methods

### Trial setting

The study will be conducted at the Pain Medicine Clinics affiliated with the Division of Pain Medicine at the University of Toronto (Toronto, Ontario, Canada), and at the Comprehensive Integrated Pain Program (Toronto Western Hospital, Toronto).

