### Recruitment

#### Feasibility of recruitment

Participants will be recruited from the Comprehensive Integrated Pain Program – Interventional Pain Service (CIPP-IPS) clinic at Toronto Western Hospital and the Pain Medicine Clinics affiliated with the Division of Pain Medicine at the University of Toronto. Around 15 patients undergo RFN of the CMBN every month at the study sites. Assuming a study enrollment rate of 50%, we should be able to recruit 7 to 8 participants every month. We expect to enroll the required sample size for the study over 9 to 12 months. There are two other academic pain centers and two community pain clinics in the Toronto area that may be approached to become study enrollment sites if the proposed enrollment is lower than anticipated.

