### Assignment of interventions

#### Randomization, sequence generation, and allocation concealment

Upon participant enrollment, patients will be randomized to one of two arms, with a 1:1 allocation. The randomization sequence will be computer-generated by a member of the research team. An independent research coordinator will handle the treatment allocation process. This coordinator will ensure allocation concealment by using sequentially numbered, sealed opaque envelopes. The allocation sequence will be provided to an attending staff pain medicine physician.

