### Statistical methods

A statistician will be consulted to assist in data analysis and interpretation. Descriptive information for the sample’s study measures will include frequency distributions or proportions for categorical variables and means (standard deviations) or medians (interquartile ranges) (if non-normally distributed) for the continuous variables. To compare data between the two groups, categorical outcomes will be analyzed with the chi-square test and continuous variables will be analyzed with independent *t*-tests (or Wilcoxon rank sum test, as appropriate). A two-sided *p*-value of < 0.05 will be considered statistically significant. Both intention-to-treat (based on study arm allocation) and per-protocol (based on the participants who adhered to the study protocol and provided data at study outcome time points) analysis will be performed and reported.

Correlation between reduction in pain and improvement in function will be evaluated with a longitudinal model of changes from baseline to 3-month, 6-month, and 12-month follow-ups. An intention-to-treat strategy will be used for all analyses. Differences in treatment effects and 95% confidence intervals for pain and secondary outcome scores will be calculated using chi-square and odds ratios for dichotomous variables, and ANOVA (with *t*-tests for pairwise comparisons) and Mann–Whitney for continuous variables, as indicated. A set of logistic regression models for categorical outcome at 3 months will be created using variables hypothesized to have an effect on treatment (gender, intensity of pain, nature of injury), as well as those found to have a *p*-value less than 0.20 in univariate analysis. A secondary analyses based on data from participants who undergo unilateral versus bilateral RFN with each of the two study treatments is also planned. Missing data will be imputed using the “last observation carried forward” approach if at least 80% of the outcome data is available for the participant. All analyses will be performed using the SPSS program.

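### The trial is multicentre, but the stated 3-month analyses carry no site term, so any between-site variance stays in the error term and costs a modest amount of precision

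*Protocol article*

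**What the plan says.** **Sites.** The Trial design section calls the study a "prospective, multicentre, active comparator-controlled, non-inferiority randomized trial with two parallel groups". Trial setting names more than one location: "The study will be conducted at the Pain Medicine Clinics affiliated with the Division of Pain Medicine at the University of Toronto", together with the pain programme at Toronto Western Hospital. Feasibility of recruitment adds that there are "two other academic pain centers and two community pain clinics in the Toronto area that may be approached to become study enrollment sites", should enrolment fall short.

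**Allocation.** Trial design states: "Randomization will occur on the day of the procedure and will be done to one of two arms on a 1:1 allocation basis". The section on randomization, sequence generation and allocation concealment repeats the ratio: "Upon participant enrollment, patients will be randomized to one of two arms, with a 1:1 allocation". Both describe a computer-generated sequence and numbered, sealed, opaque envelopes. Neither mentions site strata or blocks, and neither says that there is a single list or that the list is unstratified.

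**Analysis.** Statistical methods is explicit: "To compare data between the two groups, categorical outcomes will be analyzed with the chi-square test and continuous variables will be analyzed" by independent t-tests, or by the Wilcoxon rank sum test. Treatment differences and their 95% confidence intervals are to come from chi-square and odds ratios, ANOVA with t-tests, or Mann–Whitney. Logistic models for the categorical 3-month outcome are to include gender, pain intensity and nature of injury, plus any variable with a univariate p-value below 0.20. Site is not named. No covariate-adjusted analysis of 3-month mean NRS, the outcome used for the sample size, is stated.

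**The concern.** In a multicentre trial, participants at one site may on average do better or worse than those at another, whichever arm they are in. A two-sample t-test treats that difference as noise, whereas a model with a site factor removes it from the residual. The sample size section sets a 1-point non-inferiority margin, and Statistical methods plans 95% confidence intervals, so the width of the interval bears directly on whether non-inferiority can be shown. The article writes out no rule that sets a confidence bound against the margin; that use of the interval is inferred from the design.

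This goes beyond an omission in a condensed article. The tests are named and the model covariates are listed, and site is in neither. It could enter only through the p < 0.20 screen, and then only for a categorical outcome.

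**Working it through.** **Inputs from the Sample size section:** margin 1 NRS point, SD 1.7, 36 per arm (72 in total), 80% power, alpha 0.05, described as two-sided; 80 to be recruited for 10% dropout. **Assumed, because the article gives no figure:** two equal sites; a difference k between their mean 3-month NRS of 0, 0.5 or 1.0 points (1.5 as an upper case); true treatment difference zero; total SD held at 1.7.

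**Step 1: the plan's own figure.** n per arm = 2 × 1.7² × (z_alpha + z_power)² / 1².
- One-sided 0.05: 5.78 × (1.645 + 0.842)² = 35.7, so 36 per arm and 72 in total. This reproduces the plan.
- Two-sided 0.05, as the text states: 5.78 × (1.960 + 0.842)² = 45.4, so 46 per arm and 92 in total. This does not.
- Dropout: 72 / 0.90 = 80, which matches.

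The starting power at 36 per arm is therefore 69.2% with a 95% confidence interval and 79.6% at one-sided 0.05 (t-based). That gap is a separate matter from site, so both baselines are shown below.

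**Step 2: variance between sites.** With two equal sites the site variance is k²/4, out of a total of 1.7² = 2.89. A model with site has SE = √[2 × (2.89 − k²/4) / 36]. Power is the probability that a noncentral t with noncentrality 1/SE exceeds the critical value, on 70 df unadjusted and 69 df with site.

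| Site difference k | Share of variance | SE | 95% CI half-width | Power, two-sided 0.05 | Power, one-sided 0.05 |
|---|---|---|---|---|---|
| Unadjusted | – | 0.401 | 0.80 | 69.2% | 79.6% |
| 0.5, adjusted | 2.2% | 0.396 | 0.79 | 70.1% | 80.3% |
| 1.0, adjusted | 8.7% | 0.383 | 0.76 | 73.1% | 82.7% |
| 1.5, adjusted | 19.5% | 0.360 | 0.72 | 78.3% | 86.6% |

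For 0.5 and 1.0 points the gain is 0.9 and 3.9 percentage points on the first baseline, and 0.7 and 3.1 on the second. With k = 0 there is no gain, and one degree of freedom is spent. The 1.5-point row assumes that sites differ by more than the whole margin and should not carry the argument.

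**Step 3: error rates.** Simulation with 20,000 replicates, two equal sites and the 95% confidence interval set against the margin (nominal one-sided type I error 0.025):

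| Site share of variance | Allocation | Site term | Type I error | Power |
|---|---|---|---|---|
| 5% | not stratified | no | 0.024 | 69.3% |
| 5% | not stratified | yes | 0.024 | 70.6% |
| 5% | stratified | yes | 0.026 | 71.4% |
| 10% | not stratified | no | 0.027 | 68.9% |
| 10% | not stratified | yes | 0.025 | 73.4% |
| 10% | stratified | no | 0.021 | 70.1% |
| 10% | stratified | yes | 0.026 | 73.7% |

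Leaving site out does not raise type I error above nominal beyond simulation noise. At a 10% share, the site term alone recovers nearly all of the gain, with or without stratified allocation. If allocation is stratified and the analysis ignores it, the test becomes somewhat conservative (0.021).

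**The case against.** The strongest reply is that an unadjusted comparison in a randomised trial is valid, and that site adjustment is an efficiency gain of unknown size. The current sites are all Toronto pain clinics. Entry requires two diagnostic blocks with at least 80% relief. The radiofrequency settings are the same in both arms, and operators need at least 5 years' experience. Between-site variance may well be small, and at a 0.5-point difference the gain is under 1 percentage point of power. All of this stands and limits the size of the point. It does not remove it, because the analysis is positively stated without site and changing that costs almost nothing.

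Four stronger readings are tempting and are not supported:

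- **That the list is unstratified.** A reader might infer this because no strata are mentioned. The article condenses a full protocol that is not shown, and strata and blocks are commonly left to that document.
- **That site imbalance biases the result or produces false claims of non-inferiority.** With unstratified allocation, chance imbalance is already part of the unadjusted standard error. It is the same loss of precision, not an additional harm.
- **That site explains why power falls short of 80%.** The 69% baseline comes from the mismatch between one-sided and two-sided alpha in Step 1.
- **That each site has its own operators and patient mix, or that late-added sites will track calendar time.** The article does not tie operators to sites, and the additional clinics are only a contingency.

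**Conclusion.** The point holds as a modest loss of precision. The trial is multicentre, and the stated 3-month analyses do not use site. With two equal sites, total SD 1.7 and 36 per arm, this costs about 1 to 4 percentage points of power if sites differ by 0.5 to 1.0 NRS points, and nothing if they do not differ. The 95% confidence interval half-width would fall from 0.80 to between 0.79 and 0.76 points. The treatment estimate remains unbiased and type I error is not inflated. The size rests wholly on assumed site differences. The change is worth making because it is cheap and the interval half-width is already 0.80 against a margin of 1.

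**What to change.** Prespecify, before unblinding, a linear model for 3-month NRS with treatment and site as factors, and a corresponding model for the 50% responder outcome. Take the 95% confidence interval for the non-inferiority comparison from it. Fix in advance a rule for pooling very small sites, which matters most if more clinics join. This covers every participant, including those already randomised.

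State whether allocation is stratified by site. If it is, the site term makes the analysis match the design. If it is not, separate lists per site with varying, undisclosed block sizes can be used for future participants only, since recruitment began in March 2023.

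The cost is a few degrees of freedom and one pooling rule. If per-site lists are introduced, short blocks at a small site could be guessed by the unblinded operator, which is why block sizes must vary and stay concealed.

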## Methods

### Trial setting

The study will be conducted at the Pain Medicine Clinics affiliated with the Division of Pain Medicine at the University of Toronto (Toronto, Ontario, Canada), and at the Comprehensive Integrated Pain Program (Toronto Western Hospital, Toronto).

### Eligibility criteria

The inclusion and exclusion criteria are summarized in Table 1. A flow chart of the trial is provided in Fig. 1.

**Table 1 Tab1:** Inclusion and exclusion criteria

**Inclusion criteria**
1. Age 18 to 85 years
2. Predominant axial (non-radicular) neck pain for at least 3 months
3. 7-day average NRS score for neck pain of 5/10 or greater at baseline evaluation
4. Moderate or greater functional impairment due to pain, defined as NDI Questionnaire raw score of 15 out of 50 (30%) or greater
5. Failure to respond to conservative medical management (pharmacologic, physical therapy) for at least 3 months. 6. Positive response to two consecutive diagnostic blocks of the CMBN with a short and long-acting anesthetic, respectively, defined as reporting at least 80% relief of index pain concordant with the expected duration of the local anesthetics
**Exclusion criteria**
1. Participants with financial incentives or litigation associated with ongoing pain
2. Inability to complete assessment study-related outcome instruments
4. Widespread pain in the body
5. Prior RFN of the CMBN within the last 6 months at the time of enrollment
5. Severe mental health issues
6. Pregnancy or other reasons that preclude the use of fluoroscopy
7. Untreated coagulopathy
8. Systemic or local infection at the time of screening

**Fig. 1 Fig1:**
[figure not shown]
Study flow chart

### Interventions

#### Interventions common to both arms

Pre-procedure management will be identical for participants in the two groups and will be conducted at our interventional suites at the study sites. This includes obtaining peripheral intravenous access and application of routine electrocardiogram, non-invasive blood pressure, and pulse oximeter monitors. Oxygen by nasal prongs or mask and light sedation with midazolam and or fentanyl at the Anesthesiologist’s discretion will be provided. The RFN procedure will be performed at the same levels as identified by the diagnostic medial branch nerve blocks.

#### Study intervention and active comparator groups

*Study intervention*: Radiofrequency neurotomy of cervical medial branch nerves (CMBN) with end-on lesioning with multi-tined trident cannulae will be performed.

*Active comparator*: RFN of CMBN with parallel lesioning with sharp straight conventional cannulae (IPSIS’s technique)

The levels selected for diagnostic procedures will be determined by the treating physician based on the overall clinical picture including the location of pain, pain referral patterns, and imaging findings. The RFN parameters will be identical for the two active treatments (82° Celsius +/− 3–5° to accommodate the fluctuations that occur during ablation for 90 s), except for cannulae placement. The technique described in the SIS Practice Guidelines will be used for parallel lesioning cannulae placement [11]. For end-on placement of the multi-tined cannulae (Trident^®^, Diros Technology Inc, Markham, Ontario, Canada), the patient will be in the lateral position and the target will be the joint space between inferior articular process of C2 and superior articular process of C3 for the third occipital nerve, the middle of the facet pillars for the third to fifth cervical levels, and the superior part of the sixth and seventh cervical facets.

#### Post-procedural management

Following completion of the procedure, participants will be taken to the post-procedure recovery unit. Any complications related to the procedure will be recorded and managed if required. Participants will be discharged from the unit as per routine hospital policy. As per standard of care, participants will be advised to take one to two tablets of Percocet (containing 5 mg of oxycodone and 325 mg of acetaminophen) or Tylenol number 3 (containing 30 mg of codeine and 325 mg of acetaminophen) every 6 h if required to a maximum of 8 tablets in 24 h if they have pain intensity NRS scores higher than 3 out of 10. Frequency of use of these medications by study participants will be recorded and the average daily opioid consumption in oral morphine equivalents for the 1 week preceding the follow-ups at 1, 3, 6, and 12 months will be recorded.

In the event a subject is randomized but does not receive the trial interventions, the treatment will not be reassigned. Trial personnel will assess the patient and collect data throughout their enrollment in the trial. Participants in both arms will wear an actigraphy device (Appendix 1) to assess the quality and duration of sleep and activity for 1 week prior to the trial treatments (for collection of baseline data) and starting on the day of intervention for 1 month after to longitudinally assess the impact of the trial treatments on sleep and physical activity.

#### Modifications

The study participants have the right to withdraw from the study at any time. Any withdrawals will be documented along with the reason provided by the participant. If the reason for removal of a subject from the study is an adverse effect, the principal specific event will be recorded in the case report form. The subject will be followed until the adverse effect is resolved, if agreed by the subject.

#### Concomitant care

There will be no restrictions or changes to the baseline home medications, but study participants will be advised to avoid introduction of new analgesic agents in the post-treatment period.

#### Rescue medication and risk management

Any other pain medications provided during the study period will be considered rescue therapy. Participants will be given symptomatic treatment, and standard care will be provided. If any side effects or complications arise due to the study interventions, emergency unblinding will only occur when knowledge of the intervention is essential for medical care as determined by the Principal Investigator. In the event of emergency unblinding of one or more research team members, the timing, reason, and personnel involved will be recorded in the case record form (CRF), and blinding will be maintained for as many other trial personnel as possible.

### Outcomes

Patients will be assessed at baseline and 1, 3, 6, and 12 months after the study interventions. The assessment schedule and parameters are summarized in Table 2.

**Table 2 Tab2:** EndPaRL assessment schedule

**Outcome**	**Measure**	**Baseline**	**Immediate after procedure**	**1 month after procedure**	**3 months after procedure**	**6 months after procedure**	**12 months after procedure**
**Patient demographics**		**X**					
**Pain intensity**	NRS	**X**	**X**	**X**	**X**	**X**	**X**
**Neck disability**	NDI	**X**	**X**	**X**	**X**	**X**	**X**
**Global improvement**	PGIC			**X**	**X**	**X**	**X**
**Sleep quality**	PSQI	**X**		**X**	**X**	**X**	**X**
**Sleep duration**	In hours and minutes from actigraphy device	**X**		**X**			
**Physical functioning**	Time spent at different activity levels from actigraphy device^b^	**X**		**X**			
**Opioid intake**	Daily OME in mg	**X**		**X**	**X**	**X**	**X**
**Analgesics**	Name and dose	**X**		**X**	**X**	**X**	**X**
**Procedure** **(1) Duration** **(2) Cost** **(3) Discomfort** **(4) Radiation**	(1) In minute (2) In CAD (3) 0–10 (4) Dose in mSv		**X** **X** **X** **X**				
**Complications**	e.g., bleeding, hematoma		**X**				
**Adverse effects**				**X**	**X**	**X**	**X**
**Health-related quality of life**	EQ-5D-5L^a^	**X**		**X**	**X**	**X**	**X**

*CAD* Canadian dollars, *NRS* Numerical Rating Scale, *OME* Oral morphine equivalents

^a^EuroQol 5-level EQ-5D version (EQ-5D-5L); Neck Disability Index (NDI); Numerical Rating Scale (NRS); Patients’ Global Impression of Change (PGIC); Pittsburgh Sleep Quality Index (PSQI)

^b^Data on physical activity and sleep collected using participant-worn actigraphy devices (light/moderate/severe)

The following are the *primary outcomes*:The between-group difference in mean NRS for pain intensity scores at 3 months after the interventions.The between-group difference in the proportion of patients with a positive analgesic response (defined as 50% or greater reduction in the NRS score for neck pain as compared to baseline) at 3 months after the interventions.

The following are the *secondary outcomes*:Pain intensity: The between-group difference in mean NRS for pain intensity scores at 1, 6, and 12 months after the interventions.Incidence of analgesic response: The between-group difference in the proportion of patients with a positive analgesic response (defined as 50% or greater reduction in the NRS score for neck pain as compared to baseline) at 1, 6, and 12 months after the interventions.Neck pain-related disability: The between-group difference in the proportion of patients with a 10% or greater reduction in the Neck Disability Index (NDI) score at 1, 3, 6, and 12 months after the interventions.Participant-assessed improvement: The between-group difference in the proportion of participants reporting some or much improvement on the Patients’ Global Impression of Change (PGIC) scale at 1, 3, 6, and 12 months after the interventions.Quality of sleep and life: The between-group difference in the mean Pittsburgh Sleep Quality Index (PSQI) scores and EuroQol (EQ-5D-5L) scores at 1, 3, 6, and 12 months after the interventions. Sleep health will be assessed using PSQI, and actigraphy-measured variables respectively, including sleep duration, sleep quality, daytime sleepiness, sleep timing, and wakefulness after sleep onset.Procedure-related outcomes: The between-group difference in the duration of procedure, discomfort, radiation dose, and cost of the procedures.Actigraphy-collected physical activity and sleep: The between-group difference in the average physical activity and sleep duration as measured by wrist-worn actigraphy over 1 week prior to the procedure and 1 week prior to the 1-month follow-up after the interventions.Adverse effects of the interventions: The between-group difference in the incidence of peri-procedural complications and post-procedural adverse effects at 1, 3, 6, and 12 months after the interventions.Analgesic requirements: The between-group difference in opioid requirements as measured by daily oral morphine equivalents in milligrams averaged over the 1 week prior to the 1, 3, 6, and 12 months follow-ups after the interventions.The patient assumption of the group they were assigned to at 3-month follow-up after the study interventions

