### Objectives

The aim of our trial is to compare the efficacy of the recommended SIS technique utilizing a conventional parallel approach against the end-on approach for RFN of the CMBN in patients presenting with chronic, moderate-to-severe, neck pain in the context of cervical facet joint disease. The following are the primary objectives of this trial:To compare the difference in mean Numerical Rating Scale (NRS) for pain scores at 3 months after the study interventions.To compare the proportion of patients with a positive analgesic response (defined as 50% or greater reduction in the NRS score for neck pain as compared to baseline) at 3 months after the study interventions.

The following are the secondary objectives:To compare the difference in mean NRS for pain scores at 1, 6, and 12 months after the study interventions.To compare the proportion of patients with a positive analgesic response at 1, 6, and 12 months after the study interventions.To compare the proportion of patients with 10 points or greater reduction in the Neck Disability Index (NDI) score (the minimal clinically important difference (MCID) [8]) at 1, 3, 6, and 12 months after the study interventions.To compare the proportion of participants reporting some or much improvement in the Patients’ Global Impression of Change (PGIC) scale at 1, 3, 6, and 12 months after the study interventions [9].To compare the mean Pittsburgh Sleep Quality Index (PSQI) scores and EuroQol (EQ-5D-5L) scores at 1, 3, 6, and 12 months after the study interventions [10].To compare the duration of performing the study interventions, patient discomfort, radiation dose, and cost of the study interventions.To compare average physical activity and sleep duration as measured by wrist-worn actigraphy over 1 week before the procedure and 1-month follow-up after the study interventions.To assess the incidence of peri-procedural complications and post-procedural adverse effects during and at 1, 3, 6, and 12 months after the study interventions.To assess opioid requirements in daily oral morphine equivalents in milligrams averaged over the 1 week prior to the 1-, 3-, 6-, and 12-month follow-ups after the study interventions.To assess the patient assumption of the group they were assigned to at 3-month follow-up after the study interventions.

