#### Baseline data

Baseline data will include participants demographics, pain intensity as measured by NRS score, physical activity, sleep duration both measured by Actigraphy, sleep quality measured by PSQI, physical function as measured by the NDI, opioid and non-opioid analgesic intake.

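### The Neck Disability Index is compared between arms only as a responder proportion, which makes the function comparison less precise than the collected scores allow; add the baseline-adjusted mean difference beside it

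*Protocol article*

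**What the plan says.** Two sections of the protocol article define the between-arm NDI comparison, both as a proportion at 1, 3, 6 and 12 months. The Objectives have "To compare the proportion of patients with 10 points or greater reduction in the Neck Disability Index (NDI) score", and the secondary outcomes have "The between-group difference in the proportion of patients with a 10% or greater reduction in the Neck Disability Index (NDI) score". Neither lists a comparison of mean NDI or mean change in NDI.

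The other questionnaire scores are handled differently. The NRS is compared as a mean and as a responder rate. For sleep and quality of life, the outcome is "The between-group difference in the mean Pittsburgh Sleep Quality Index (PSQI) scores and EuroQol (EQ-5D-5L) scores". PGIC is compared as "the proportion of participants reporting some or much improvement".

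NDI is a numeric score: Table 1 sets an entry criterion "defined as NDI Questionnaire raw score of 15 out of 50 (30%) or greater". Table 2 schedules it at baseline and at every follow-up visit. The Baseline data section names its role: "physical function as measured by the NDI". The Statistical methods assign tests by type of variable: "categorical outcomes will be analyzed with the chi-square test and continuous variables will be analyzed with independent" *t*-tests, or a rank test as appropriate.

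**The concern.** The Hypotheses section claims non-inferiority on function, listed first among the secondary domains. In Table 2 and the outcome list, actigraphic activity is compared only up to the 1-month visit. (The Follow-up data section names actigraphy in a general list for all visits, but no later actigraphy outcome is defined.) EQ-5D-5L is a generic quality-of-life measure. NDI is therefore the only function-specific outcome at 3, 6 and 12 months.

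Reducing a numeric score to a yes/no classification treats a patient just past the threshold like one far past it, and a patient just short of it like one who got worse. The between-arm comparison becomes less precise. With about 36 patients per arm, true non-inferiority on function is then harder to show, and a real deficit with end-on lesioning is easier to miss. The scores for a sharper comparison are already being collected. A minimal clinically important difference is a good reason to report responders, but it does not require that the arms be compared on the cut alone.

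**Working it through.** **Inputs from the protocol article (Sample size, Statistical methods).** 36 per arm, 1:1; two-sided 0.05; NRS margin 1 point; NRS SD 1.7.

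**Assumptions.** No NDI SD, effect, responder rate or margin is given. I work in SD units, take NDI as roughly normal with equal SDs, and borrow the NRS ratio 1/1.7 = 0.588 SD as the reference shift, with smaller shifts alongside.

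**The plan's own figure.** n per arm = 2 × SD² × (z_α + z_β)² / margin², with 2 × 1.7² = 5.78.
- One-sided 0.05: 5.78 × (1.645 + 0.842)² = 35.7, so 36 per arm, as stated.
- Two-sided 0.05: 5.78 × (1.960 + 0.842)² = 45.4, so 46 per arm. At 36 per arm, power is about 70%.
- Dropout: 72 / 0.90 = 80, as stated.

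The stated n matches the one-sided level. That is a separate matter; it explains why the continuous-score power below is about 69% and not 80%.

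**Power on the score.** Noncentrality = shift × √(36/2). At 0.588 SD this is 0.588 × 4.243 = 2.496; the two-sided *t*-test on 70 degrees of freedom has 69.2% power.

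**Power on the cut.** With responder rate p in the parallel arm, the end-on rate under the same shift is Φ(Φ⁻¹(p) − shift). For p = 50% it is Φ(−0.588) = 27.8%; for p = 80% it is 60.0%. Chi-square power comes from exact binomial probabilities at 36 per arm.

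| Shift (SD) | *t*-test on score | Chi-square, responders 40-80% | Loss (points) |
|---|---|---|---|
| 0.667 | 80% | 56-60% | 20-24 |
| 0.588 | 69% | 47-49% | 20-22 |
| 0.4 | 39% | 24-27% | 12-15 |
| 0.3 | 24% | 15-17% | 7-9 |
| 0.2 | 13% | 9-11% | 3-4 |

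If 90% of the parallel arm respond, chi-square power at 0.588 SD is 37%, a loss of 32 points. A lenient threshold makes the loss larger.

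**Sensitivity to the one-sided level.** At one-sided 0.05 and 0.588 SD, with the cut midway between the arms, the normal approximation gives 80.3% against 62.8%, a loss of about 17 points.

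**Precision, with no assumed effect.**
- 95% half-width for the mean difference: 1.96 × √(2/36) = 0.46 SD.
- 95% half-width for the responder difference at a 50% rate: 1.96 × √(0.5/36) = 0.231. Dividing by the normal density at the median, 0.399, gives 0.58 SD.
- The median cut keeps 2/π = 64% of the information, equivalent to about 36 × 0.64 = 23 patients per arm.

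**The case against.** **The Statistical methods leave room for a mean comparison.** They promise effect estimates with intervals for pain and secondary outcome scores, *t*-tests or Mann-Whitney for continuous variables, and a longitudinal model involving function. This does not answer the point. Those sentences assign methods by variable type, and the listed NDI outcome is dichotomous. The longitudinal model is described as relating pain reduction to functional improvement, not as comparing arms. The article also fixes the outcome definition in two places, so this is a stated choice and not detail left to an analysis plan.

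**The power figure is conditional.** This stands. A reader might infer that the cut costs 20 points of power in any event. The documents do not support that: 0.588 SD is borrowed from another instrument, the protocol expects similar efficacy, and the loss is only 3-4 points at 0.2 SD for responder rates of 40-80%.

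**The responder outcome is clinically readable and tied to a cited MCID.** This also stands. A reader might infer that it should be demoted, or that no guideline supports it. Demotion is not needed, and the reference list is not shown, so its support cannot be judged.

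**Other stronger readings.** A fixed 10-point drop is a different share of a low and a high baseline score, but that applies only if raw points are meant; the Objectives and Outcomes disagree on points or percent and must be reconciled in their own right. No power loss can be stated for PGIC, because its number of categories is not given. Nor does the cut favour end-on lesioning in a non-inferiority reading: a wider interval makes the claim harder. Finally, these are secondary outcomes, and the primary NRS mean comparison is unaffected.

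**Conclusion.** The point holds in a limited form. The plan fixes a less efficient between-arm comparison for its main function questionnaire, unlike its handling of NRS, PSQI and EQ-5D-5L. That the cut loses information does not depend on which NDI threshold is meant, but the amount lost does. Under rough normality and a shift of 0.588 SD, power at 36 per arm falls from about 69% to 47-49% for responder rates of 40-80%. The loss is smaller for smaller effects and larger when most patients pass the threshold. The practical consequence is a wider interval for a secondary non-inferiority hypothesis; the main result and sample size are not at risk. A worthwhile and inexpensive improvement.

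**What to change.** In the Objectives and in the secondary outcomes, add the between-group difference in mean NDI score at 1, 3, 6 and 12 months, adjusted for baseline NDI, with a 95% CI. Keep the MCID responder proportion as a listed outcome beside it.

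The cost is one extra model per visit and one more secondary comparison. No new data, visits or patients are needed.

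Optionally, also report PGIC on its full ordered scale with the Mann-Whitney test that the Statistical methods already name, next to the proportion improved.
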